## Abstract

**Introduction:**

Few autistic adults are able to integrate successfully into the world of work given their difficulties adapting to the social and stressful aspects of work environments. Interpersonal synchrony, when two or more individuals share body movements or sensations, is a powerful force that consolidates human groups while promoting the ability to self-regulate and cooperate with others. The abilities to self-regulate and cooperate are crucial for maintaining a calm and productive work environment. This study protocol outlines research that aims to assess the effects of group interpersonal synchrony on prosociality and work-related stress of young autistic adults in their work environment.

**Methods and analysis:**

This mixed-methods randomized controlled trial will investigate two movement-based group synchronous and non-synchronous intervention conditions. The sample will be composed of young adults enrolled in an innovative Israeli program designed to integrate cognitively-abled 18- to 25-year-old autistic adults into the Israeli army work force. The movement-based intervention sessions will take place in groups of 10–14 participants, once a week for 10 weeks. Questionnaires, behavioral collaborative tasks and semi-structured interviews will be conducted. Quantitative data will be collected for each participant at three points of time: before and after the intervention period, and 17 weeks after the end of the intervention. Qualitative data will be collected after the intervention period in interviews with the participants.

**Discussion:**

Little is known about interventions that promote successful integration into social and stressful work environments. The findings are likely to shed new light on the use of group interpersonal synchrony in autistic individuals at work.

**Trial registration:**

NCT05846308.

## Introduction

Individuals diagnosed with Autism Spectrum Disorder (ASD) have difficulties related to social interaction and communication, as well as repetitive and stereotyped interests [1]. According to the DSM-V [1] cognitively-abled autistic people are characterized by a high intellectual level and the least requirements for support. There are few cognitively-abled autistic adults who can successfully integrate into the world of work since they often manifest atypical behavior in social situations, find it hard to initiate social interactions, have limited interest in forming social relationships, find it challenging to cooperate with co-workers and often fail to regulate work-related stress [2–4]. The ability to work, according to the International Classification of Functioning, Disability and Health (World Health Organization, 2001) is considered to be a significant factor affecting individuals’ health, quality of life, and wellbeing. This accounts for the growing interest in developing tailored interventions to promote the long-term integration of challenged populations into social and stressful work environments [5, 6].

A new wave of research in autism suggests that in addition to difficulties with social interactions and stressful environments, ASD is also characterized by fundamental differences in sensorimotor functioning including the delayed development of motor skills [7], abnormal gait [8], difficulty with balance [9], difficulties in coordinating movements that involve both sides of the body, and in controlling force and direction when throwing a ball [10]. These altered modes of perceiving and moving in the world (alone, as well as with other people) may help explain some of the key fundamental social impairments in autism and asynchronous social behavior in particular [11–15]. Asynchronous social behavior in autism (e.g., reduced eye contact, absence of well-timed co-regulation, no coherent engagement of mutual attention, no anticipation and no emotional build up in shared interactions) was first identified in a micro-analytic study of videos of an 11-month old infant who was diagnosed with ASD during her second year of life [16]. Stronger evidence for the association between atypical interpersonal synchrony and autism was recently described [13] in a study which also suggested that there may be a disruption in intrapersonal mechanisms such as atypical motor timing, and in interpersonal mechanisms such as atypical inter-individual coupling.

The aim of this trial is to assess the effects of group interpersonal synchrony on the prosociality and work-related stress of young autistic adults in their work environment. The trial is designed as a randomized controlled trial with two parallel groups (experimental group and treated control group), primary and secondary endpoints and a follow-up of intervention effectiveness after 17 weeks as described in Fig 1. Randomization will be performed as block randomization with a 1:1 allocation. In the following sections we review research on interpersonal synchrony in autism and on the associations between interpersonal synchrony, prosociality and work-related stress.

**Fig 1 pone.0307956.g001:**
[figure not shown]
Schedule of enrolment, interventions and assessments. Note: EHQ, Edinburgh Handedness Questionnaire; NTB, Need to Belong Scale; IOS, Inclusion of Other in Self Scale; FCI, Friendship Closeness Inventory; GSB, General Sense of Belonging Scale; IS, Irritation Scale; CT, Collection Task; PGG, Public Goods Game.

### Interpersonal synchrony in autism

Interpersonal synchrony is said to occur when two or more individuals are engaged in body movements or sensations (such as gaze, affect, voice and touch) at the same time (precise synchrony) or as a responsive behavior (lagged synchrony) [17, 18]. This form of interpersonal relationship has at times been called “togetherness”, especially when there is no leader or follower in this form of non-verbal behavioral sharing [19]. Body movements may be connected spatially (spatial synchrony), temporally (rhythmic synchrony) or qualitatively (effort synchrony) [20, 21]. Interpersonal synchrony can emerge intentionally as a result of an explicit shared goal, such as running at same pace, or spontaneously without being aware of it as part of a social interaction, such as when dancing, singing or playing an instrument [22]. Studies over the last ten years have shown that autistic children and adults demonstrate poor ability to synchronize their body with a partner during rhythmic interaction activities and games [11, 12, 23–26]. For example, an innovative study focusing on motion synchronization during an open-ended joint improvisation paradigm dubbed the Mirror Game found that cognitively-abled autistic adults exhibited much less interpersonal synchronization than neurotypical individuals [23]. Autistic adolescents also presented less interpersonal synchrony, and fewer intentional and spontaneous motor interactions on a pendulum coordination paradigm [12].

### The effects of interpersonal synchrony on prosociality

Prosociality refers to behaviors that are intended to benefit others, such as helping, cooperating, sharing and donating [27]. Recently, there has been increased interest in studying the causal influences of interpersonal synchrony on prosociality in general [28, 29] and specifically in work environments [30, 31]. A meta-analysis of 60 studies that compared an interpersonal synchrony condition to at least one control condition found a medium-sized effect of interpersonal synchrony on the prosociality of neurotypical adults with regard to both attitudes and behavior towards individuals or groups involved in the same intervention [28]. Another meta-analysis of 42 studies suggested that synchrony in larger groups increases prosociality [29]. Other studies that have assessed the effects of interventions based on mirroring movement in autistic adults suggest that interpersonal synchrony may be an effective intervention tool for enhancing social skills [32] and specifically emotional inference [33], which is a fundamental skill underlying prosociality. Manders et al. [34] argued that the structured mirroring task, which encourages interpersonal synchrony such as in the case of the Mirror Game, may not be sufficient to effectively support social engagement in autistic individuals, since they tend to simply follow the instructions to synchronize their movements. These findings emphasize the need to include synchronized sensory-motor interactions in tailored interventions to foster prosociality, while proposing both structured intentional synchrony and less structured spontaneous synchrony [35]. To the best of our knowledge, no study has examined the effectiveness of group interpersonal synchrony on the prosociality of autistic individuals in the context of a social work environment. Since working teams’ cognitive performance declines in stressful environments [36], in the following section we review research on the associations between interpersonal synchrony and work-related stress.

### The effects of interpersonal synchrony on work-related stress

Work-related stress is defined as individuals’ responses when presented with work demands and pressures that are misaligned with their knowledge or abilities and which challenge their ability to cope [37]. A recent longitudinal field experiment in a neurotypical work environment found that a 9-week synchronous movement intervention reduced work-related stress and diminished sick days immediately following the intervention, but not after three months [30]. A qualitative evaluation of workplace choir singing in Health Service staff reported greater enjoyment at work and an improvement in work engagement [31]. One possible explanation is that participating in synchronous activities may release endogenous opioids such as endorphin, which are involved in the regulation of emotional pain [38]. While these studies support the widespread belief that togetherness and harmony only have beneficial effects on personal wellbeing, a study by Galbusera et al.’s [39] suggested that interpersonal synchrony when implemented in the form of a dyadic moving task designed to encourage spontaneous social interaction, could decrease people’s ability to self-regulate due to their extra reliance on the dyadic interaction. This may imply that an effective intervention to support autistic individuals in stressful work environments should include co-regulation with others in a group setting rather than in an intimate dyadic framework that might be less efficient in terms of stress regulation. To the best of our knowledge, no studies have examined the effectiveness of interpersonal synchrony on the work-related stress of autistic individuals in the context of a group.

### The effects of interpersonal synchrony on social closeness and a sense of belonging

According to McNeill’s [40] Muscular Bonding hypothesis, group interpersonal synchrony, which involves coordinated rhythmic movement, is a powerful force uniting human groups and enhancing social closeness and a sense of belonging. Social closeness is defined as the way individuals engage in friendships, interact and relate to significant others [41]. Social closeness in a workplace setting was enhanced using an intervention in which participants shared synchronous movement [30]. Sense of belonging is the experience of personal involvement in a system or environment, which makes individuals feel that they are an integral part [42]. Interpersonal synchrony has been found to enhance people’s sense of belonging in an experimental setting using a finger tapping task [43]. Furthermore, these feelings of social closeness and belongingness among individuals are known to promote prosocial behavior [44] as well as the ability to cope with various stressors [45].

### Moderating factor underlying the effects of interpersonal synchrony

The need to belong is characterized by the drive to be noticed, valued and accepted by others [46]. It is a fundamental need that exerts a strong influence in virtually every domain of social behavior starting early in development [47]. While all individuals differ in the strength of their desire to belong to social groups, the social motivation hypothesis argues that autistic individuals’ need to belong is diminished because they find social stimuli less rewarding as compared to neurotypicals [4]. For example, Brezis et al. [23] found that autistic adults who played the Mirror Game with an expert improvisor were less likely to want to continue playing, but their ratings of how they felt during the game did not differ. Hence, group interpersonal synchrony may be more effective when the need to belong is higher, since the intrinsic motivation is likely to have a positive effect on the sense of belonging to the group. The suggested moderating model is depicted in Fig 2.

**Fig 2 pone.0307956.g002:**
[figure not shown]
Theoretical moderating model of interpersonal synchrony.

### Objectives

The aim of this study is to assess the effects of group interpersonal synchrony on the prosociality and work-related stress of young autistic adults in their work environment. The primary objective is to determine whether a synchronized group intervention will have an immediate and/or long-term positive effect on participants’ prosociality and work-related stress. The secondary objectives are to determine: (1) Whether a synchronized group intervention will have an immediate and/or long-term positive effect on participants’ social closeness and sense of belonging, (2) Whether this effect will be influenced by participants’ need to belong as reported before the intervention, (3) How participants perceive the intervention as affecting their prosociality and work-related stress, and (4) In what ways the participants’ perception will contribute to a better understanding of the intervention effect.

## Materials and methods

A convergent mixed methods design will be applied, where quantitative and qualitative data are collected and analyzed in parallel. The use of mixed methods may provide a better understanding of the study objectives. Specifically, a convergent design will be used [48] to gain a more in-depth understanding of the quantitative results by incorporating the participants’ qualitative perspectives. The two sets of results will be compared to obtain a more complete understanding of the study objectives by validating one set of findings with the other and ensuring that the participants’ perspectives are consistent and not dependent on the research method.

### Participants

This study will be conducted in collaboration with *Roim Rachok* Program (RRP) an innovative Israeli civilian program designed to integrate cognitively-abled young autistic adults first into the Israeli army work force, and later into the labor market [6]. As part of the program, before joining the army, the trainees take part in a professional 13 weeks course delivered by an interdisciplinary team that includes army officers and instructors, an occupational therapist, a speech therapist and an art therapist. The course content is composed of two main fields: (a) army related professional instruction (e.g., software programming, data analysis and image interpretation), and (b) integration into the army working environment. Trainees who successfully complete the course are inducted into the army as civilian volunteers for a four-month trial period. The trial period is designed to allow trainees to experience their future working environment before committing to long-term army service. Trainees who successfully complete the trial period can sign up for one more year of service with an annual option of extension, for up to three years. The RRP participants are integrated into the army corps with other soldiers who do not have developmental disabilities.

The sample for this study will be comprised of young adults enrolled in an RRP who fulfill the following criteria: **Inclusion criteria:** (a) Aged 18 to 25 when accepted to the program, since these age limits are defined as part of the admission requirements for the RRP. (b) Diagnosis of autism spectrum disorder: Participants must have an official diagnosis of an autism spectrum disorder as assessed by a child psychiatrist or clinical psychologist according to the DSM-V [1] before acceptance to the RRP. **Exclusion criteria:** Trainees with severe sensory impairments such as blindness or deafness and/or severe physical disability.

### Ethical considerations

This study has been approved by the ethics committee for human experiments of the Faculty of Social Welfare and Health Sciences at the University of Haifa (Approval # 017/21). Participation in the study will be voluntary without preconditions. All participants will receive a letter explaining the study and how it will be conducted, and will sign an informed consent form to participate in the study. Participants who have custodian will be required to present a written custodian approval as well. No risks or discomfort are expected as a result of participation in this study. However, if any physical or emotional discomfort is experienced, the participants will receive appropriate support from the RRP professional staff. The data will be coded to protect the participants’ confidentiality. All data, including the questionnaires, the behavioral task outcomes and audio recordings will be stored in a secure cloud and will not be available to anyone other than the research team. The audio recordings will be deleted immediately after being transcribed.

### Sample size

A meta-analysis on prosocial consequences of interpersonal synchrony among neurotypical adults found a medium-sized effect of interpersonal synchrony on prosociality with regard to both attitudes and behavior towards individuals or groups involved in the same intervention [28]. Therefore, an effect defined as d = 0.25 may be expected [49]. An a-priori power analysis using the G*Power computer program [50] indicated that a total sample size of 40 participants would be needed to detect medium-sized effects defined as f = 0.25, with 80% power and alpha at .05, using a repeated measure, within-between interaction ANOVA with four groups and three measurements. We will recruit at least N = 60 participants (30 in each intervention group) to plan for possible dropouts.

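### The expected effect is stated as d = 0.25 but the sample size is computed for f = 0.25, so the 80% power does not apply to the effect that the plan says it expects

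*Protocol article*

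**What the plan says.** The Sample size section of the protocol article starts from a meta-analysis in neurotypical adults that "found a medium-sized effect of interpersonal synchrony on prosociality with regard to both attitudes and behavior". It gives no number from that source, and continues: "Therefore, an effect defined as d = 0.25 may be expected".

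The next sentence reports that "a total sample size of 40 participants would be needed". The target entered in the power program is given there as "medium-sized effects defined as f = 0.25, with 80% power and alpha at .05". The calculation assumes four groups and three occasions, and tests the group-by-time interaction. On recruitment the section adds: "We will recruit at least N = 60 participants (30 in each intervention group) to plan for possible dropouts".

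No correlation between measurements, effect pattern over time or dropout rate is given. The Introduction and Study design describe two parallel arms allocated 1:1. The Data analyses section tests the primary objective with a two-way mixed ANOVA, that is, arm by time.

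**The concern.** The two sentences treat d and f as one index because both are labelled 0.25 and both are linked to a medium effect. Cohen's d is a difference between two means in SD units. Cohen's f is the SD of the cell effects over the within-cell SD. For two equal groups f = d/2, so f = 0.25 corresponds to d = 0.5, twice the d that the text expects. For a group-by-time interaction the gap between a post-baseline difference and f is wider still.

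What is at stake is how a null result will be read. A reader who takes the paragraph at its word will think the trial had 80% power for the effect its authors expected, and may count a null result as evidence against synchrony. The documents do not support that inference.

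**Working it through.** **Inputs from the article.** Expected d = 0.25; f entered = 0.25; alpha 0.05; power 80%; k = 4 groups and m = 3 measurements in the calculation; N = 40 needed, 60 recruited; two arms randomised.

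**Assumptions not in the article.** Correlation between measurements ρ = 0.5 (varied below) and sphericity ε = 1.

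**Formula** (noncentral F, within-between interaction, as in G*Power):
λ = f²·N·m/(1 − ρ), df1 = (k − 1)(m − 1), df2 = (N − k)(m − 1).

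**Step 1. Reproduce the plan's figure.** f = 0.25, k = 4, m = 3, N = 40, ρ = 0.5: λ = 0.0625 × 40 × 3/0.5 = 15.0, df = 6 and 72, power 80.5%. At N = 36 it is 74.9%. So N = 40 reproduces, and the 80% belongs to f = 0.25. With k = 2 the same f would need N = 28, and N = 40 would give 93.5%.

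**Step 2. Take d = 0.25 literally, with f = d/2 = 0.125.** At ρ = 0.5, λ = 3.75 (N = 40) or 5.625 (N = 60).

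| Groups | Power, N = 40 | Power, N = 60 | N for 80% |
|---|---|---|---|
| 4, as entered | 23% | 36% | 152 |
| 2, as randomised | 38% | 54% | 106 |

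With two arms, over ρ = 0 to 0.8, power runs from 21% to 77% at N = 40 and from 30% to 92% at N = 60.

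**Step 3. Take d as an arm difference arising after baseline.** Randomised arms have no expected baseline difference. Let the arm difference be 0 at baseline and D at both later visits.
- Its mean over time is 2D/3, so the interaction effects in one arm have absolute size D/3, D/6 and D/6.
- Their mean square is (D²/9 + D²/36 + D²/36)/3 = D²/18, so f = D/√18.
- The pattern (0, D, 0) gives the same f.
- D = 0.25 gives f = 0.059. D = 0.5 gives f = 0.118.
- Conversely, f = 0.25 corresponds to D = 0.25 × √18 = 1.06 SD.

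Power with two arms:

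| D (SD) | N | ρ = 0 | 0.3 | 0.5 | 0.7 | 0.8 |
|---|---|---|---|---|---|---|
| 0.25 | 40 | 8% | 10% | 12% | 16% | 23% |
| 0.25 | 60 | 10% | 12% | 15% | 23% | 33% |
| 0.5 | 40 | 19% | 25% | 34% | 53% | 72% |
| 0.5 | 60 | 27% | 37% | 49% | 72% | 89% |

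**Step 4. Difference detectable with 80% power, two arms.** Solving for D gives D = √(6λ(1 − ρ)/N), where λ is the value giving 80% power: about 10.0 at N = 40 and 9.9 at N = 60. At ρ = 0.5 and N = 60, D = √(6 × 9.88 × 0.5/60) = 0.70.

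| N | ρ = 0.3 | 0.5 | 0.7 | 0.8 |
|---|---|---|---|---|
| 40 | 1.03 SD | 0.87 SD | 0.67 SD | 0.55 SD |
| 60 | 0.83 SD | 0.70 SD | 0.54 SD | 0.44 SD |

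All of this is at alpha 0.05, before the Holm correction and before any allowance for clustering in the intervention groups. At the first Holm step over the three primary outcomes (alpha 0.05/3, ρ = 0.5) the detectable difference becomes 1.00 SD at N = 40 and 0.81 SD at N = 60.

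**The case against.** The best defence is that d is a slip of the pen. Both figures are linked to a medium effect, both are 0.25, the calculation uses f, and N = 40 follows correctly from it. On that reading the 80% is delivered for the target actually entered, and the low powers for d = 0.25 fall away because nobody meant d = 0.25. This is plausible, and the article cannot settle it. It stands against any claim that the arithmetic itself is wrong.

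It does not clear the paragraph. If d was meant to be 0.5, or if f = 0.25 is read as the usual medium standardised difference, a medium difference appearing after baseline is an interaction f of only 0.118, with 34% or 49% power at ρ = 0.5.

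A second objection also stands in part. The correlation of 0.5 and the (0, D, D) pattern are assumptions made here, and the results depend strongly on ρ. At ρ = 0.8, with all 60 analysed, power for D = 0.5 is 89%. The same ρ lifts the f = 0.125 reading to 92%. The retest figure of .86 under Social closeness concerns a secondary scale, so it does not fix ρ for the primary outcomes, but it shows that 0.5 is not the only reasonable value. No single power figure should therefore replace the present one.

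A reader might also infer from D = 1.06 SD that the trial can see only effects near 1 SD. That does not follow. The 1.06 SD is f = 0.25 translated to two arms, where power at ρ = 0.5 is 93.5% at N = 40 and about 99% at N = 60. The 80% limit at that correlation is 0.87 or 0.70 SD.

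**Conclusion.** The paragraph is wrong as written. It names one effect, sizes the trial for another, and nothing else in the article reconciles them. The calculation for f = 0.25 is sound. The error lies in attaching its 80% to an expected d = 0.25, or to a medium effect without qualification.

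At ρ = 0.5 with two arms, power for d = 0.25 is 38% to 54% under f = d/2, or 12% to 15% as a post-baseline difference (N = 40 to N = 60). For the post-baseline reading it stays at or below 33% for any ρ up to 0.8. For d = 0.5 after baseline it is 34% to 49%, and it passes 80% only with a high correlation and all 60 analysed. The 20 extra participants are meant to cover dropout and cannot be relied on to close the gap.

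These sizes rest on the assumed correlation, sphericity and effect pattern. They do not show that the trial is uninformative, only that the stated power is unsupported for the stated effect.

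**What to change.** Keep N = 60. According to Study status, three cycles are complete and the fourth is in progress, so this is a correction of what is claimed, not of recruitment.

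- Correct the d/f sentence and say which effect was meant.
- Give the expected effect on one scale, as a between-arm difference in change in SD units, for the two-arm analysis that will be run.
- State the assumed pattern over time and the assumed correlation, and show the conversion to the interaction f.
- Report power and the 80% detectable difference over a range of correlations, for 60 analysed and for 40, as tabulated above.
- Note that the figures precede the Holm correction and clustering.
- Drop the unqualified claim of 80% power for a medium effect.

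The cost is one rewritten paragraph and a less favourable stated power. No participants are added, and neither conduct nor analysis changes.

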#### Quantitative data analysis

The data obtained as study variables will be coded, processed and analyzed at the end of the collection process. IBM SPSS Statistics Version 27 will be used for statistical analysis. To control the family-wise error rate when performing multiple hypothesis tests, Bonferroni Step-Down (Holm) procedure will be applied. Participants must attend at least 4 sessions to be included in the analyses. To describe the sample, descriptive statistics will be calculated followed by univariate and bivariate statistical analyses. The first step will be to assess whether the data follows a normal distribution for each of the variables which will guide the choice of parametric or non-parametric tests. To answer the primary study objective and the first secondary study objective, the effects of the intervention over time (at the end of the intervention and after 17 weeks) will be examined using a two-way mixed model ANOVA. To explore the second secondary study objective, the influence of the need to belong on the effect of the intervention over time (at the end of the intervention and after 17 weeks) will be examined using a three-way mixed model ANOVA.

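### The sample size of 40 was computed for a four-group, 6-df interaction, but the planned primary test is a two-arm, 2-df interaction; the stated N and power do not describe it, though the error is on the safe side

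*Protocol article*

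**What the plan says.** The Sample size section says that "a total sample size of 40 participants would be needed" for a medium effect of f = 0.25, "with 80% power and alpha at .05", "using a repeated measure, within-between interaction ANOVA with four groups and three measurements". It then raises the target to at least 60, 30 per intervention group, to allow for dropouts. It does not define the four groups, and it gives no correlation between occasions and no sphericity correction.

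Elsewhere the design has two arms. The Introduction describes "two parallel groups (experimental group and treated control group", and Study design compares one synchronous with one non-synchronous condition.

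Quantitative data analysis plans two kinds of test. For the primary objective and the first secondary objective, the effects over time "will be examined using a two-way mixed model ANOVA". For the second secondary objective, the influence of need to belong "will be examined using a three-way mixed model ANOVA". Holm's procedure controls the family-wise error rate, and Table 2 lists three primary outcomes. Study design splits need to belong into high and low.

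**The concern.** A sample size statement should describe the test that answers the primary question. Here the number of groups entered does not match the number of arms, so the numerator degrees of freedom, the required N and the power all belong to another test.

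The four groups may be the 2 x 2 cells of arm by need-to-belong level. In that case the test that was powered is a pooled cell-by-time comparison, which the plan does not run. At stake is whether readers can rely on 40 as the number needed, on 80% as the power of the primary test, and on the step from 40 to 60 as a dropout margin. A reader could also take the 80% to cover moderation, for which it was not computed.

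**Working it through.** **Inputs.** From Sample size: f = 0.25, alpha = 0.05, power 80%, three occasions (m = 3), four groups. From the Introduction and Quantitative data analysis: two arms, two-way mixed ANOVA. Assumed, because the article gives neither: correlation between occasions rho = 0.5 and sphericity (epsilon = 1). Ranges are shown below.

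**Formula.** Noncentral F for the within-between interaction with k groups, in the G*Power parameterisation:

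- lambda = f² × N × m / (1 − rho)
- df1 = (k − 1)(m − 1)
- df2 = (N − k)(m − 1)

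With the inputs above, lambda = 0.0625 × N × 3 / 0.5 = 0.375 N. N is rounded up to equal group sizes.

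**Step 1: reproduce the stated figure.** k = 4, N = 40: lambda = 15, df = 6 and 72, power 80.5%. At N = 36 it is 74.9%. So 40 is the correct answer for four groups, and four groups was evidently what was entered.

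**Step 2: the planned primary test.** k = 2, so df1 = 2.

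| N | lambda | df | power |
|---|---|---|---|
| 28 | 10.5 | 2, 52 | 81.2% |
| 40 | 15.0 | 2, 76 | 93.5% |
| 60 | 22.5 | 2, 116 | 99.1% |

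The required N is 28.

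**Step 3: sensitivity to the assumptions.**

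| Assumption | N, two groups | N, four groups |
|---|---|---|
| rho 0.3 | 38 | 56 |
| rho 0.5 | 28 | 40 |
| rho 0.7 | 18 | 28 |
| rho 0.5, epsilon 0.75 | 34 | 48 |

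The two-group N is the smaller in every row.

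**Step 4: alpha after Holm.** The strictest step for three primary outcomes is 0.05/3 = 0.0167. With rho = 0.5, the two-arm interaction then needs N = 36, and power is 86% at 40 and 97% at 60.

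**Step 5: the three-way term.** With need to belong at two levels, the 6 df of the four-cell by time interaction split into arm by time, need-to-belong by time and the three-way term, with 2 df each. Moderation is the three-way term alone, with df = 2 and 2(N − 4). Its power depends on what share of the interaction effect it carries:

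- If f = 0.25 applies to this term itself, power is 93.5% at 40 and 99.1% at 60.
- If f = 0.25 is the pooled four-cell effect, 80% power needs lambda of about 10.05 at N = 40, a share of 10.05/15 = 67%. At N = 60 it needs about 9.90, a share of 9.90/22.5 = 44%.
- As an illustration only, suppose that just the synchronous, high-need participants change. The share is then one third, lambda is 15/3 = 5.0 at N = 40 and 22.5/3 = 7.5 at N = 60, and power is 49% and 68%. For rho from 0.3 to 0.7 the ranges are 36% to 72% and 52% to 89%.

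**The case against.** The strongest reply is that nothing was miscalculated: 40 is right for the inputs entered, and four groups has a visible source in the 2 x 2 cells of the moderator analysis. The mismatch is also conservative, since 40 exceeds the 28 that the primary test needs, and no design decision changes. Most of this stands. The four-cell layout does occur in the plan; only the pooled 6-df test does not. The article never makes the link, however, and on that reading the stated N was not computed for the primary objective at all.

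Three stronger readings are tempting, and the documents support none of them.

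- **The trial is underpowered because of this error.** At the stated f, the two-arm test needs fewer participants than the four-group test in every row of the sensitivity table.
- **Moderation falls short of 80%.** The article states no power for moderation and introduces that analysis as exploratory. The 49% and 68% figures rest on a one-cell pattern that it does not state; its section on the moderating factor says only that the intervention may work better when need to belong is higher. Nor must the three-way term carry the whole effect to reach 80%: about two thirds is enough at 40.
- **The target could be cut to 28.** This ignores Holm. It also ignores that the same section says "an effect defined as d = 0.25 may be expected" next to f = 0.25. For two groups d = 0.25 corresponds to f = 0.125, which gives 54% power at N = 60 under the same assumptions. That is a separate point, but it argues against spending the apparent surplus.

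**Conclusion.** The point holds as a wrong or undefined basis for the stated sample size, not as a shortfall. The pair of 40 participants and 80% power describes a 6-df four-group interaction that appears in neither planned analysis. For the primary two-arm interaction, the same inputs give N = 28 and power of 93.5% at 40 and 99.1% at 60. These figures assume rho = 0.5 and sphericity. For rho from 0.3 to 0.7 the two-arm N runs from 38 to 18, against 56 to 28 for four groups, so the direction does not depend on the assumption. The conclusion that the error is conservative is conditional on f = 0.25. The power of the moderation term cannot be read from the article in either direction.

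**What to change.** In the Sample size section:

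- Define the four groups, or correct them to two, and name the interaction that was powered.
- Restate N and power for the two-arm by three-occasion interaction, giving the assumed correlation and sphericity.
- Show the figures at the alpha that applies after Holm: at 0.05/3, with rho = 0.5, N = 36 and 86% power at 40.
- State that the 80% was not computed for the 2-df three-way moderation term, whose power depends on the share of the effect it carries. Any one-cell figures should be labelled as an illustrative assumption.
- Keep the target of 60.

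The cost is one recalculation and a few reworded sentences. No participants are added and no analysis changes.
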